### Guidelines for stopping the trial early

There are no statistical reasons specified for stopping the trial early. The Chair of the TSC reviewed all serious adverse events. The trial would be stopped early to prevent harm, if there were an undue number of related SAE. The TSC also considered any relevant safety data, any recommendations for early closure of the study on this basis would had been based on their expert opinion, there were no formal statistical criteria specified for stopping the trial early.

## Timing of final analysis

All analyses will be performed at the end of the follow-up period, once all data are either collected or data from any participants with outstanding outcome data is declared missing as agreed by the Chief Investigator and Statisticians.

## Timing of outcome assessments

Outcome assessments will be performed at baseline, 16 weeks (end-of-therapy assessment) and 28 weeks (follow-up assessment) although there is no strict window for outcome assessments.

# Statistical Principles

## Confidence intervals (CI) and level of statistical significance

As this is a feasibility study, the emphasis will be on producing relevant data summaries.. For consideration of potential proof-of-efficacy investigations (i.e., Positive and Negative Syndrome Scale (PANSS) Total score, Psychotic Symptom Rating Scales (PSYRATS), Questionnaire about the Process of Recovery (QPR) and Brief Core Schema Scale (BCSS)), two-sided 100*(1-α)% confidence intervals with α ranging from 0.05 to 0.25 (in steps of 0.05) will be computed [3], thus reporting adjusted point estimates and confidence intervals (CIs), ranging from 75% to 95% confidence, for the effect obtained from the analyses described in section 7.2. This approach is based on a minimally-important difference (MID) between trial arms and is therefore more appropriate than formal hypothesis testing when a study is underpowered.

The MID for the PANSS total score can range between 4 and 21 points [4] [5]. Due to lack of literature to select appropriate MID for the PANSS and the rest primary outcome candidates, we define a promising effect to be around a standard effect size of 0.3 (or more) [ref]. In addition, we will consider an absolute change of 5 points in the Total PANSS scores as a promising effect.

Two-sided 95% confidence intervals will be presented for the estimates of the treatment effects of all other continuous outcomes. No formal testing will be performed and, as a result, p-values will not be presented.

## Adherence and protocol deviations

### Adherence

Adherence to the intervention relies upon both therapist and participant factors.

a) Participant adherence

Participant adherence to the iMAPS-2 intervention will be measured by the number of therapy sessions attended by the participants allocated to the intervention arm. An individual will be classed as having attended a session if they attended a part or the whole of a session (defined as a minimum duration of 15 minutes). We will report the mean (SD) number of sessions attended or median (IQR), as appropriate. We will also summarise the number (%) of adherent participants with a 95% exact (binomial) confidence interval (for the %). If a participant attends 5 or more of the 12 sessions [4], then they will be deemed adherent.

b) Therapist fidelity

Therapist fidelity will be assessed by:

i) Rating a sample of audio recordings of therapy sess ions using the Cognitive Therapy Rating Scale Revised (CTS-R) or the Cognitive Therapy Rating Scale for Psychosis (CTS-Psy). Scale scores will be summarised as mean (SD) if they are (approximately) symmetrically distributed or median (IQR) if they are asymmetrically distributed.

ii) Therapists who are part of the research team (approximately 4 therapists) will complete the iMAPS fidelity scale after each therapy session to record the contents of each session in terms of: agenda targets; between-session activities/home tasks; the techniques used. Items within each domain of the fidelity scale will be summarised as follows:

**Agenda targets**

1. Is there a target Image? (yes/no)
2. Distress re image (0-100)
3. Impact on Functioning (0-100)
4. Is there an Agenda? (at least 1 item included)

We will obtain the frequency (%) of all sessions where both a target image is present and there is an agenda with at least 1 item included. Distress image and Impact on functioning will each be summarised by mean (SD) or median (IQR) as appropriate.

**Between-Session Activities(BSA)/Home tasks**

1. Last session BSA reviewed as part of agenda? YES/NO
2. Has it been COMPLETED? YES/NO
3. Current session BSA agreed (collaboratively)? YES/NO
4. Last session therapist BSA reviewed as part of agenda? YES/NO
5. Has it been COMPLETED? YES/NO
6. Current Session Therapist BSA set? YES/NO

We will obtain frequencies (%) of all sessions where:

- The previous session home task was reviewed
- The previous session home task was completed
- A new session home task was set

And report them separately for the client (items 1 to 3) and therapist (items 4 to 6).

**Technique sessions (Yes, took place in session or NO, did not)**

1. Assessment and Engagement
2. Imagery Problem List
3. iMAPS Psychological Formulation (This could be with either the maintenance formulation, longitudinal formulation or both)
4. Psychoeducation regarding power of imagery
5. Normalising the image
6. Safe Place Image
7. Image Suppression
8. Behavioural Experiments
9. Upsetting Memories – Transformation
10. Upsetting Memories – Running image past the worst point
11. Upsetting memories – updating aspects of the image
12. Emotional bridge to past (diagnostic imagery exercise)
13. Imagery rescripting – past events
14. Imagery rescripting – flashforwards
15. Imagery rescripting – discussion of negative beliefs re self and others, schemas
16. Working with night-time imagery - Updating aspects of the image, rescripting new endings
17. Creating Positive Imagery – generating positive images

We will obtain the frequency (%) of all sessions by technique used.

### Protocol deviations

We will present a listing of all the protocol deviations occurred during the trial by treatment group with details of the type of deviation recorded. No formal statistical analysis will be undertaken.

## Analysis populations

Feasibility analyses will include all the consented participants to estimate the proportion of eligible consented participants and eligible participants randomised. To summarise the number of iMAPS-2 therapy sessions attended, we shall include all the participants allocated to the intervention group. The proportion of adherent participants (attending at least 3 sessions of the iMAPS-2 therapy) will include all the participants allocated to the intervention group.

Analyses of efficacy will be by intention-to-treat (ITT), where all randomised participants for whom outcomes are available will be analysed in their allocated group regardless of their adherence to therapy.

The safety population will also follow the ITT principle and it will comprise all randomised participants.

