## Trial procedures

Service users who meet eligibility criteria and are under the care of the NHS Trust, will be invited to complete a number of measures at baseline, 16 weeks and 28 weeks follow ups. The service user will meet with a research assistant at the time intervals above to complete an integrated interview and a number of self-report measures. In addition to face to face appointments, the assessments may be conducted via NHS approved MS TEAMS or Attend Anywhere “Telehealth” video platforms. At the same time as giving consent to take part in the main trial and randomised to either usual care and iMAPS therapy or usual care, participants will be able to consent to being contacted by another researcher on the project, (via their preferred method) to provide additional information about the qualitative interviews which could take place at any point from end of therapy to end of study.

Figure 1. Participant Timeline

Potential participants are contacted by their care -coordinator or self refer to the research team, check meet initial eligibility criteria, given PIS, at least 24hrs to consider taking part, then re-contacted

RA arranges to receive informed written consent and undertake eligibility screen. Feedbacks outcome.

If eligible, appt to complete baseline outcome measures

30 participants are randomised to iMAPS therapy and usual care

15 participants are randomised to usual care

RA meets with participants 16 weeks post randomisation to complete outcome measures

Staff and patients who agreed to take part in interviews contacted and interviews arranged throughout this period

RA meets with participants 28 weeks post randomisation to complete outcome measures

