## Recruitment

(Strategies for achieving adequate participant enrolment to reach target sample size)

The Chief Investigator will support Research Assistants to visit clinical services to present the trial, engage clinicians in the trial and to provide copies of the participant information sheets and posters. Members of the clinical care team will seek consent from potential participants to be contacted by the researchers. Service users/patients who consent for details to be passed to the trial team, will be given a Participant Information Sheet (PIS) by either a member of the care team, by post/email or by the RA and given the opportunity to ask any questions they may have. The RA will contact the service user/patient at least 24 hours (often longer) after being given the PIS to discuss whether they would like to take part in the study. The Service User will be given the opportunity to ask any further questions they may have and will be offered time to consider taking part should they wish. Individuals who give informed, written consent will be screened for eligibility. Individuals who are eligible, complete the assessment and are randomised will enter the trial.

iMAPS-2 will also accept self referrals from Service Users at Pennine care NHS FT, in Boroughs which the trial is actively recruiting from. Posters will be displayed in NHS mental health services to advertise the study. A study website will also be available. Participant information sheets will also be available, but the main aim of the website is public engagement and dissemination. If an individual self refers, we will ask their consent to contact their mental health team/mental health professional involved in their care to check eligibility criteria and obtain information for risk assessment purposes and to ensure participation is not contraindicated.

The key screening is for the reporting, of distressing image related to a psychotic experience which would score 3 or above on PANSS P1 or P3 in a brief discussion with the patient. The RA will then complete an eligibility review with the PI. After the eligibility review, the potential participant will be contacted by the RA to inform them of whether they are eligible to participate in the study.

During the consent and eligibility screening meeting, the member of the research team will complete the following measures with the participant;

- Demographic Information
- Participant Details (contact information, GP, etc)

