## Consent And eligibility

Service Users/Patients who are recruited via the clinician-referral recruitment route, will hear about the study from their clinician, who will take to them about the study and discuss the trial with them. Any questions will be answered, they will be given a participant information sheet (PIS) and will be asked to give their consent to be contacted by the research team and to pass on risk information to allow a risk assessment. A research assistant will communicate with clinician colleagues to identify potential participants, be passed on contact details for potential participants, and we will ask the clinician a number of risk questions to ensure we have complete risk assessment documentation. The research assistant will then contact potential participants directly to talk about the study with them and answer any queries about participation.

There is also a self-referral route to participation. In these instances, the research assistant will gain clear informed verbal consent to contact their care co-ordinator (CCO)/clinician involved in their care to establish if they meet criteria to take part (inclusion criteria) and to share risk information to complete a risk assessment. The research assistant will also contact the care team to explore if they have any concerns regarding the service user/patient’s participation and their capacity to consent to take part. If the service user/patient may potentially meet the inclusion criteria for the trial and has an ongoing interest in taking part, the research assistant will contact them to arrange a meeting to take their informed consent and undertake the eligibility screen.

Service Users/Patients interested in taking part will have as long as they wish (while the trial is open to recruitment) to think about the information sheet before being contacted by a member of the research team, with at least 24 hours. The Participant Information Sheet (PIS) outlines what participants are asked to do, how their information will be utilised, and the risks and benefits of taking part in the trial.

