At the first appointment with the service user/patient interested in taking part, the research assistant will check they have been given a PIS and had a chance to review it. The service user/patient will have another opportunity to re-read it and have any further questions answered. It will be reiterated to all service users/patients interested in taking part that participation is voluntary and that their usual care and treatment will not be impacted if they decline to take part. The right to withdraw and not take part anymore will also be reiterated and any withdrawal will have no impact on their care and treatment.

Those who wish to participate, will give written informed consent. The original wet-ink signed copy of the consent form(s) will be retained in the Investigator Site File and a copy given to the participant. A copy of the consent form will be sent to the participants relevant care team to be on their clinical records (or a copy directly uploaded to the care record). Screening assessment for eligibility will then take place. If eligible, the initial assessment will be undertaken and the participant will be randomised. Participation in the study will begin. A similar process will be followed for referrers or clinicians or therapists who are taking part in an interview study (with the exception of not uploading copies/sending copies of consent forms to their medical records or writing to their GPs to inform them of their participation in the study). After each assessment timepoint is completed by the RA, we will contact the participant by phone 48 hours later to check on their wellbeing and ensure they are fine after the appointments.

A research assistant will determine (with support from the Chief Investigator [name]) if a participant has capacity to give informed consent and meets inclusion criteria. All researchers working on the study will attend the NIHR training on good clinical practice and informed consent.

Trained RAs will assess each participant’s capacity at each assessment interval (baseline, 16 weeks, 28 weeks and qualitative interviews where relevant) to determine whether the participant still qualifies as having capacity and thus is still able to provide informed consent to continue. However, the participant will not be required to sign further consent forms.

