# Trial Population

## Screening data

We will produce a CONSORT flow diagram [5]. The upper section of the CONSORT flow chart will include;

- Number of patients referred to the study.
- Number of patients screened.
- Number of potentially eligible patients contacted
- Number of patients recruited (i.e., consented)
- Number of participants recruited but not eligible, along with reasons for exclusions.
- Number of eligible participants.
- Number of eligible participants not recruited, along with reasons for non-recruitment.

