## Analysis methods

**Objective 1.** What number and percentage of eligible patients/service users consent to the trial (recruitment)?

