**Outcomes**

- Number of patients referred to the study.
- Number of patients (potential participants) contacted
- Number of patients screened for eligibility.
- Number of patients screened but not eligible, along with reasons for non-eligibility or withdrawal of interest.
- Number of eligible patients.
- Number of eligible patients not recruited, along with reasons for non-recruitment
- Number of participants recruited (consented).
- Source of recruitment
- Number of participants randomised.

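### Objective 1 asks what share of eligible patients consent, but neither the feasibility proportions in SHEAP 5.3 nor the one Objective 1 percentage with an interval is a consent rate

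*Combined protocol and SAP*

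**What the plan says.** **The question.** The protocol (Objectives and Research Questions) and the SHEAP (Aim and objectives; 7.2, Objective 1) open with the same question: "What number and percentage of eligible patients/service users consent to the trial (recruitment".

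**The order of steps.** Protocol 3.4 states: "Individuals who give informed, written consent will be screened for eligibility". Protocol 3.6, having described written consent, continues: "Screening assessment for eligibility will then take place". The image-distress ratings and the key PANSS questions are listed for that consent and screening meeting. Provisional checks come earlier. Figure 1 in protocol 3.3 has "check meet initial eligibility criteria, given PIS" before consent. Protocol 3.5 has staff apply the entry criteria when identifying candidates. For self-referrals, 3.6 makes the consent meeting depend on a provisional judgement: "If the service user/patient may potentially meet the inclusion criteria for the trial".

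**The analysis.** SHEAP 5.3 reads: "Feasibility analyses will include all the consented participants to estimate the proportion of eligible consented participants and eligible participants randomised". SHEAP 6.1 lists the flow-chart counts, equates recruited with consented, and includes "Number of eligible participants not recruited, along with reasons for non-recruitment". The Objective 1 outcome list in SHEAP 7.2 includes "Number of eligible patients not recruited, along with reasons for non-recruitment". The Objective 1 analysis gives exact binomial 95% intervals for randomisation rates, to be judged against a progression criterion whose denominator is the recruitment target (green from 36 of 45).

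**The result.** The text above Supplementary Table 1 restates the consent question and reports 45 randomised out of a target of 45: 100%, 95% CI 92% to 100%.

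**The concern.** A consent rate needs people who said no in its denominator. The set in SHEAP 5.3 contains none, and the percentage with a stated interval measures attainment of target. The counts that could supply a consent rate are planned elsewhere in the SHEAP, but under labels that can be read in more than one way and with no ratio attached. The denominator would therefore be chosen after the data are in hand.

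The consent rate sets how many patients have to be approached to fill a definitive trial. That is a main reason for asking the question in a feasibility study, and target attainment cannot supply it.

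**Working it through.** **1. The plan's own figure.** Inputs: 45 randomised, target 45. With x = n the exact (Clopper-Pearson) lower limit is 0.025^(1/n) = 0.025^(1/45) = 0.921. The result is 100% (92.1% to 100%), which matches the reported interval. The monthly counts in Supplementary Table 1 also sum to 45. The figure is correct as randomised / target. Neither its numerator nor its denominator counts eligible patients or consent decisions.

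**2. What SHEAP 5.3 can estimate.** Take C consented, E of them confirmed eligible and R randomised. The named proportions are E/C and R/E. Both can vary. Assuming E = 45, since the total consented is not given:

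- C = 50: 45/50 = 90% (78% to 97%)
- C = 60: 45/60 = 75% (62% to 85%)
- C = 90: 45/90 = 50% (39% to 61%)

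These describe yield at screening. The number of decliners, D, appears in neither ratio.

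**3. What the question needs.** This is C / (C + D) among potentially eligible patients contacted. D is not given. Assume C = 45, the smallest number compatible with 45 randomised, so that every consenter was eligible and randomised and E/C and R/E are both 100%:

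- D = 5: 45/50 = 90% (78% to 97%)
- D = 15: 45/60 = 75% (62% to 85%)
- D = 45: 45/90 = 50% (39% to 61%)
- D = 90: 45/135 = 33% (25.5% to 42%)

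Patients contacted per consenter go from 50/45 = 1.1 to 135/45 = 3.0, while both 5.3 proportions and the 45/45 figure do not move.

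**4. Whether the listed counts settle it.** The two lists differ in order. SHEAP 6.1 puts screening before contact and consent before eligibility. SHEAP 7.2 puts contact before screening, and eligibility before consent. Neither says whether *eligible* is provisional or confirmed. *Recruited* also shifts: SHEAP 6.1 equates it with consented, while protocol 3.11 ties the recruitment rate to both consent and randomisation, and the results text applies the criterion to people randomised. The eligible-but-not-recruited count then has four readings:

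- provisional eligibility, recruited = consented: the decliners that the question needs;
- provisional eligibility, recruited = randomised: decliners, screen failures and later losses mixed together;
- confirmed eligibility, recruited = consented: empty, because confirmation follows consent;
- confirmed eligibility, recruited = randomised: losses between screening and randomisation, with no refusal of consent among them.

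Only the first reading serves Objective 1, and the SHEAP does not select it.

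**The case against.** The strongest reply is that this is a gap in wording and that no information is lost. Eligibility is checked provisionally before consent. SHEAP 6.1 and 7.2 plan counts of patients referred, contacted, screened, consented, and eligible but not recruited, with reasons. The proposed flow diagram in protocol Appendix 1 has boxes for people who decline. A consent rate among potentially eligible patients contacted follows from the 6.1 list by one division. Consented participants are the proper set for the two proportions that 5.3 names. No progression rule depends on the consent percentage, and the sample of 45 rests on precision for retention and the SD.

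All of that stands, and it limits the point. It also rules out some stronger readings. A reader might infer that the plan will report 100% consent by construction. Consent among the eligible inside the 5.3 set would indeed be E/E, but the SHEAP never says to compute it there. A reader might infer that eligibility is unknown until consent, but the provisional checks contradict this. A reader might infer that refusals went unrecorded or unreported. The counts are planned and the flow-diagram figure is not shown in the text available, so that cannot be concluded.

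The reply does not supply a stated ratio, a definition of *eligible*, or an analysis set that includes decliners. The results text also answers the question with a different quantity.

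**Conclusion.** The point holds as a mismatch between the first research question and the analysis specified for it. The set in SHEAP 5.3 yields screening yield and randomisation yield. The only Objective 1 percentage with an interval method is target attainment, reported as 45/45. A consent rate can probably be computed from planned counts, but it is not specified, and its denominator depends on an undefined term.

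The size cannot be fixed from the documents. With 45 consenters and an assumed 5 to 90 decliners the rate lies between 90% and 33%, a 135/50 = 2.7-fold difference in patients to contact. These decliner numbers are assumptions and not estimates for this trial. The 240 in protocol Appendix 1 cannot replace them: it is labelled as people assessed for eligibility, so 45/240 = 18.8% is neither consent among contacted nor consent among eligible. The progression decision is unaffected.

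**What to change.** In SHEAP 5.3 and 7.2 (Objective 1), report three proportions in the order the protocol follows, each with an exact 95% CI:

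- (a) consented / potentially eligible patients contacted, with decliners in the denominator;
- (b) confirmed eligible / consented and screened;
- (c) randomised / confirmed eligible.

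Widen the 5.3 set to all potentially eligible patients contacted for (a). Define *potentially eligible* as having passed the checks made before consent. Replace the eligible-but-not-recruited count with two counts: *potentially eligible, declined consent* and *confirmed eligible, not randomised*. Put the lists in SHEAP 6.1 and 7.2 in one order. Keep 45/45 as the result for the progression criterion, labelled as attainment of target, and give (a) as the answer to the consent question.

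The cost is wording and a few divisions on counts already planned. The drawback is that (a) rests on provisional eligibility, since decliners never reach the confirmatory screen, and it will be a less favourable figure than the 100% now shown against the question.
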